### Secondary outcomes

The following secondary outcomes use data from initial client exit telephone interviews:Proportion of clients recommended a LAPM by their provider.How well clients felt providers listened to their needs, measured on a four-point Likert scale: (1) listened well, (2) listened quite well, (3) did not listen well or (4) did not listen at all well.The degree to which clients felt the methods recommended by providers were relevant to their needs, measured on a four-point Likert scale: (1) very relevant, (2) a bit relevant, (3) not very relevant or (4) not at all relevant.How well clients felt they understood the potential side effects of their chosen method, measured on a four-point Likert scale: (1) understand very well, (2) understand quite well, (3) do not understand well or (4) do not understand at all well.How clients felt about the amount of information given to them during counselling sessions, measured on a five-point Likert scale: (1) much too little, (2) slightly too little, (3) about right, (4) slightly too much or (5) much too much.How clients felt about the length of their counselling sessions, measured on a five-point Likert scale: (1) much too short, (2) slightly too short, (3) about right, (4) slightly too long or (5) much too long.How clients rated their experience of receiving counselling, measured on a five-point numeric scale where 1 was “bad” and 5 was “good”.

The following secondary outcomes use data from client 4-month telephone interviews:Proportion of adopters or switchers who chose a LAPM following their FP counselling session and reported still using the same method at 4 months.Proportion of adopters or switchers who chose a LAPM following their FP counselling session and who report that they plan to continue using their current method.Proportion of clients who chose any short-acting FP method following their FP counselling and reported still using the same method at 4 months.Proportion of clients who chose any short-acting FP method following their FP counselling and who report that they plan to continue using their current method.How clients rated their overall satisfaction with the FP method they chose following their FP counselling at 4 months, measured on a five-point numeric scale where 1 was “bad” and 5 was “good”.

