**Methods/design:**

We will conduct a two-armed, parallel, cluster randomised control trial across all MSI clinics (clusters) in Ethiopia (24) and Vietnam (11), randomising 18 clinics to the intervention group and 17 to the control group. Intervention providers will attend a two-day DCA-use training programme, and use DCA in their FP counselling sessions. Usual care providers will counsel clients as before. We aim to recruit 75 clients who have had FP counselling per clinic (2625 total), following them up via two telephone interviews, initially within 2 days and then at 4 months. The primary outcome is defined as the proportion of clients who report choosing a LAPM following FP counselling and will include switchers (FP counselling clients who switch from using any other FP method) and adopters (FP counselling clients who adopt any FP method having not previously been using one). We will also collect secondary outcomes at the initial follow-up (including the proportion of clients reporting being recommended a LAPM by a provider and a range of measures of client experience and satisfaction) and at the 4-month follow-up (including a range of measures of continuation rates for different FP method types). In the intervention arm, we will also conduct mixed-methods sampling to assess how providers use DCA (using an observational survey of provider–client interactions), and understand users’ experiences of receiving and giving DCA-based FP counselling (through in-depth interviews).

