In recognition of these factors, the intervention aims to support the uptake of modern methods through quality client-centred counselling. The intention is to standardise the quality of care in FP counselling to inform clients and empower them to select their preferred method. We hypothesise that DCA will offer a more client-focused counselling process, increasing providers’ consideration of clients’ circumstances and needs, reducing bias in provider recommendations, limiting discussion of all possible FP methods but expanding discussion on client-preferred methods (as ranked by DCA) designed to suit clients’ needs and preferences. This is anticipated to improve users’ counselling experience and increase clients’ readiness to consider and accept a LAPM. Our primary objective is, therefore, to evaluate the effects of DCA on LAPM uptake among clients attending FP counselling at MSI clinics in Ethiopia and Vietnam. We will also explore any effect of the DCA-led client-centred counselling on continuation rates of LAPM uptake, since providers are actively prompted to provide an upfront discussion of the side effects in advance of LAPM uptake compared to traditional counselling. The trial is also supported by a qualitative exploration of providers’ and clients’ experience of DCA, to identify where and how DCA can be improved.

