The application gathers basic information on the client, their medical eligibility and their lifestyle, and at the end of the process provides a list of recommended methods based on the information provided, with those best fitting the clients’ responses listed at the top. The provider is then encouraged to discuss the pros and cons of the top three ranked methods with the client to explore the clients’ preferences and to help them make a decision about which contraceptive method best fits their lifestyle and needs. DCA has been designed to base its ranking of methods on clients’ fertility intentions and how effective (with regard to failure rates) the method is. The application also reflects the methods available at each centre. The application is not designed to explicitly promote the uptake of LAPM, but DCA’s intention is to offer client-centred counselling responsive to clients’ needs, which we expect to lead to an increased uptake of LAPM as more suitable and effective methods for many women’s FP needs. This means DCA is designed to prompt the provider to identify each client’s fertility intentions, medical eligibility and individual preferences, and inform each client of the possible side effects and complications of methods deemed by DCA most suitable to them. Side effects and complications are commonly left undiscussed, and so we also seek to explore if client-centred counselling and an upfront discussion of the barriers to uptake have any effect on clients’ continuation rates. Providers using DCA will discuss the most suitable methods with the client (including misconceptions, side effects and benefits) and thereby increase clients’ readiness and likelihood of accepting a suitable LAPM option (which offers greater effectiveness).

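### The two 4-month plan-to-continue outcomes refer to the client's current method rather than the one she chose, and on the natural reading all four continuation comparisons condition on a choice that DCA is expected to change

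*Protocol article*

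**What the plan says.** The Secondary outcomes section of the protocol article lists four continuation outcomes from the 4-month telephone interview.

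- LAPM, method use: adopters or switchers "who chose a LAPM following their FP counselling session and reported still using the same method at 4 months".
- LAPM, plan: adopters or switchers "who chose a LAPM following their FP counselling session and who report that they plan to continue using their current method".
- Short-acting, method use: "Proportion of clients who chose any short-acting FP method following their FP counselling and reported still using the same method at 4 months".
- Short-acting, plan: clients "who chose any short-acting FP method following their FP counselling and who report that they plan to continue using their current method".

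The next item in the same list is tied to the chosen method: "How clients rated their overall satisfaction with the FP method they chose following their FP counselling at 4 months". Table 1 repeats the current-method wording for both plan outcomes.

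The Abstract describes this group of outcomes as "a range of measures of continuation rates for different FP method types". The Background gives the purpose: "We will also explore any effect of the DCA-led client-centred counselling on continuation rates of LAPM uptake". The Intervention section says DCA aims at client-centred counselling, "which we expect to lead to an increased uptake of LAPM as more suitable and effective methods". Statistical analyses compares every outcome between arms as a risk difference and applies two-sided 5% tests to all of them.

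**The concern.** There are two separate issues.

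The first is the referent of the plan outcomes. A plan to continue the current method says something about the chosen method only if the two are the same. A client who chose an IUD, had it removed and intends to stay on pills fails the LAPM method-use outcome but meets the literal LAPM plan outcome. A client using no method has no current method, so the outcome cannot be scored for her.

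The second is the comparison between arms. If the denominator is clients who chose a LAPM (or a short-acting method), membership is decided after randomisation, by the very decision that DCA is expected to influence. The choosers in the two arms may then be different kinds of clients. The difference in continuation would mix any effect of DCA on continuation with a change in who is being followed.

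At stake is the answer to a stated exploratory question, whether this style of counselling affects continuation. The primary outcome is not affected.

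**Working it through.** **The plan's own figure.** The only related calculation in the protocol is the power statement in Sample size: 40% against 50.5%, coefficient of variation k = 0.2, 18 and 17 clinics, 75 clients each, 5% level. The cluster-level variance is p(1-p)/75 + k²p².

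- Control: 0.24/75 + 0.04 × 0.16 = 0.0096.
- Intervention: 0.249975/75 + 0.04 × 0.255025 = 0.01353.
- SE = √(0.01353/18 + 0.0096/17) = 0.0363, and 0.105/0.0363 = 2.89.
- A noncentral t with 33 degrees of freedom gives 80.2% power.

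The stated 80% reproduces. The present point concerns definitions and does not touch it, but the 40% and 50.5% are used below.

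**Current against chosen method.** The protocol gives no continuation rates, so these are assumptions. Let c be the share of choosers still on the chosen method, s the share of the others who are using another method, and p = 0.90 the share of users who plan to continue whatever they use.

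- Literal outcome: cp + (1-c)sp.
- Chosen-method outcome: cp.
- Gap: (1-c)sp, which is never negative.

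| c | s | Literal | Chosen method | Gap (points) |
|---|---|---|---|---|
| 0.80 | 0.25 | 76.5% | 72.0% | 4.5 |
| 0.80 | 1.00 | 90.0% | 72.0% | 18.0 |
| 0.95 | 0.25 | 86.6% | 85.5% | 1.1 |
| 0.95 | 1.00 | 90.0% | 85.5% | 4.5 |

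This is a shift in level. It becomes a shift in the arm difference only if leaving the method, or moving to another, differs between arms.

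**Conditioning on the choice.** Use the protocol's uptake figures and suppose DCA changes no client's own continuation. Of 50.5 LAPM choosers per 100 switchers and adopters in the intervention arm, 40 would have chosen a LAPM anyway and 10.5 are extra, which is 10.5/50.5 = 20.8%. Let the first group continue at rate a and the extra choosers at rate b (both assumed).

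- Control, among choosers: a.
- Intervention, among choosers: (40a + 10.5b)/50.5.
- Difference: 0.208 × (b - a).

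| a | b | Intervention, among choosers | Difference (points) | On the chosen LAPM at 4 months per 100 switchers and adopters, intervention vs control |
|---|---|---|---|---|
| 90% | 50% | 81.7% | -8.3 | 41.3 vs 36.0 |
| 90% | 90% | 90.0% | 0 | 45.5 vs 36.0 |
| 90% | 95% | 91.0% | +1.0 | 46.0 vs 36.0 |
| 95% | 50% | 85.6% | -9.4 | 43.3 vs 38.0 |
| 95% | 80% | 91.9% | -3.1 | 46.4 vs 38.0 |
| 95% | 95% | 95.0% | 0 | 48.0 vs 38.0 |

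The conditional comparison can favour control, favour DCA or show nothing, although no client's continuation was altered. The last column does not condition on LAPM choice.

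**The case against.** Several points on the other side have force.

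- A reader might infer that all four outcomes mis-measure continuation. The documents do not support that. The two method-use items require the same method at 4 months and validly describe continuation among choosers; for them the only issue is reading the arm difference as a causal effect.
- The conditional denominator is not certain. The primary outcome is worded as a proportion of switchers and adopters who choose a LAPM, with all switchers and adopters below the line. Read in parallel, the LAPM continuation items could be joint proportions (chose a LAPM and still use it), which would not condition on LAPM choice, although switcher or adopter status is itself settled after counselling. The Abstract's description as rates for different method types favours the conditional reading. Both readings remain open, which is a reason to state the denominators.
- A reader might infer that DCA is bound to look harmful on continuation. That needs extra choosers who continue less. The protocol gives no such rates, and DCA's prompting of side-effect discussion could work the other way. That DCA changes who chooses is also a hypothesis; if it does not, this selection does not arise.
- A reader might infer that covering adopters or switchers for LAPMs but all clients for short-acting methods is a flaw. Each outcome is compared between arms, no LAPM versus short-acting contrast is planned, and the difference causes no bias by itself.
- The 4-month form is not shown. It may put the plan question only to clients still on the chosen method, and a similar inflation in both arms would largely cancel in the risk difference. That limits the likely size, but the stated definition still counts the wrong clients and still leaves non-users unscored.

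**Conclusion.** The point stands in two parts. The wording of the two plan outcomes is a definite fault: they name the current method where the neighbouring items name the same or the chosen one. Taken literally they can only equal or exceed the intended figure among clients who can be scored, by about 1 to 18 points under the assumed rates. The conditioning is an interpretive fault. On the natural reading, a between-arm difference of about -9 to +1 points could appear with no effect of DCA on any client's continuation. That range rests on the protocol's 40% and 50.5% uptake and on assumed continuation of 90% or 95% for those who would choose a LAPM anyway and 50% to 95% for the extra choosers; it is zero when the two groups continue alike. These are secondary outcomes serving an exploratory question, but they are to be tested at 5% and so should be repaired before analysis.

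**What to change.** - Redefine both plan outcomes as still using the chosen method at 4 months and planning to continue it. Count clients who stopped, including those using nothing, as no.
- State the denominator of each of the four continuation outcomes explicitly.
- Add one outcome over all counselled clients: chose a LAPM and is still using it at 4 months. Say how clients renewing an existing LAPM are counted.
- Present the rates among choosers as descriptive and do not interpret their arm differences as causal effects of DCA on continuation.

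The cost is small: revised definitions in the protocol and analysis plan, made before the data are analysed. The method chosen, whether it is still used at 4 months and the plan to continue are already needed for existing outcomes, so little or no new data should be required, subject to checking the 4-month form. The small downside is that the added outcome combines uptake with continuation and does not isolate the latter, so it belongs beside the descriptive rates and does not replace them.

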### Provider observation checklist outcomes

The outcomes for the provider observation checklist consist primarily of closed-ended options to observed actions relating to a range of desirable provider behaviours, including those relating to clearly and sensitively explaining important information about the counselling session and FP methods available, and interpersonal skills and general conduct. The observation survey will also record the number of methods recommended to clients, the method type chosen by clients and the length of counselling sessions.

### Sample size

Based on logistical considerations, we assume that we can recruit 75 clients per clinic across 35 clinics during the recruitment period. Based on routine MSI clinic data, we estimate that the primary outcome of LAPM uptake in switchers and adopters is currently typically around 40%. We, therefore, estimate that we will have 80% power to detect an absolute increase in LAPM uptake from 40% to 50.5% (judged by trial researchers and MSI FP experts to be a sufficiently small, clinically important difference for these contexts) at a 5% level of statistical significance, assuming a between-cluster coefficient of variation of 0.2 (based on prior MSI routine data), with 18 clinics in the intervention arm and 17 in the control arm, and 75 clients recruited per clinic [20].

### Provider observation survey sample size

We based the sample size for our provider observation survey on being able to estimate all our proportional outcomes with a precision (95% confidence intervals) no wider than ±10 percentage points (i.e. assuming the least precisely estimable proportion of 0.5), which for an assumed design effect of 2 requires 193 observations. Logistically, we have resources to observe 14 providers, and we, therefore, plan to conduct 196 observations, split between eight providers in Ethiopia and six in Vietnam (14 observations per provider).

### Randomisation, allocation concealment and masking

For the main trial, all 35 clinics across Ethiopia and Vietnam will be randomised by MSI (ER) simultaneously via a computer program to either the intervention or control arm in a restricted 18:17 (intervention : control) ratio, following recruitment of providers in clinics and after obtaining provider consent. It will, therefore, be possible to conceal treatment arm allocation from providers and clients, but during the trial it will not be possible to blind (mask) either providers or clients to treatment allocation, given the explicit nature of the intervention components (e.g. following treatment allocation, intervention providers will be trained, provided with tablets and use DCA to counsel clients, and clients will be taken through the DCA counselling process). However, data collectors (telephone interviewers) will be blinded to the allocation of clients. For the provider observation survey, we will subsequently select, via simple random selection, eight providers in Ethiopia and six in Vietnam, from all participating clinics.

### Quantitative data collection and management

As MSI client data currently collected by clinics are not available for research, we prepared data collection tools to collect the required outcome data. There will be three data collection processes, all conducted by researchers. First, to collect data on our quantitative primary and secondary outcomes, as well as a range of relevant socio-demographic covariate data, researchers will conduct initial client exit telephone interviews using a data collection form. Second, researchers will also collect additional client outcome data 4 months after their FP counselling sessions on related secondary outcomes via further telephone interviews using another data collection form. Third, researchers will record outcomes from the structured provider observation survey via a structured observational checklist tool.

Data management will initially be the responsibility of the in-country study leaders. For each data collection process, an SPSS database will be created with consistent coding and design, and this will be duplicated for use across countries. The databases will then be collated and merged by the study statistician, and checked for quality, accuracy and completeness using standard data validation methods, such as range and logic checks. Errors, anomalous values and missing values will then be explored along with in-country MSI staff against original data forms, to clean and correct the databases where possible before the database is locked. No personally identifying data will be collected in any data collection process, and so all stored client data will be anonymous. Consent forms will, however, be linkable to client data in the databases via a generic ID, and so will be stored in secure locked cabinets. Given the nature of the intervention and the very low risk of harms, it was decided not to have a data monitoring committee for the trial.

Both MSI (ER) and the University of Leeds (JW, JPH and LAB) will have full access to the final trial and associated study datasets, although only the University of Leeds will be involved in analysing the data.

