### Participants, recruitment and consent

We will invite all MSI clinics in Ethiopia (24) and Vietnam (11) to participate in the study, via the respective MSI in-country directors. All providers will be invited to participate, and we will seek verbal informed consent from providers for their participation, but only those passing an assessment of their knowledge of the intervention at the end of the intervention training will be eligible to continue to participate.

Eligible participants will be women aged 18–49 years old who present at MSI clinics and receive FP counselling. During the recruitment phase of the trial, we will recruit participants across all participating clinics as they present consecutively for FP counselling, until clinics reach their target sample size. Clients attending MSI clinics for FP counselling will initially be asked, either by the receptionist or by the provider (if there is no receptionist), if they can be contacted by a researcher via telephone in the next 2 days who will ask them some questions about their experience of the study. Those who agree will then be telephoned in the next 2 days by a researcher for an exit interview. The researcher will then seek formal verbal informed consent from the client to conduct the exit interview and provide outcome data for the trial. They will also be asked if they can be contacted again at 4 months for a follow-up interview. Those clients who agree will then be contacted at 4 months after their FP counselling session by a researcher, again via telephone. Again they will first seek formal verbal informed consent for the interview before collecting the 4-month follow-up data. At both the initial and 4-month telephone interviews, clients who agree to be contacted but who do not answer their phone or are otherwise busy will be contacted again twice more over subsequent days, before being recorded as lost to follow-up. For clients lost to follow-up, their anonymous basic demographic data along with their choice of FP method will be collected from their clinic’s routine records (see Section 2.13 on statistical analyses for details of which patients will be included in the analyses). Clients will not receive remuneration for their time.

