How relevant clients felt the method(s) recommended by providers were to their needs	1–8
How well clients felt they understood the potential side effects of their chosen method	1–3, 5–6, 8
How clients felt about the amount of information given to them during counselling sessions	1–8
How clients felt about the length of their counselling sessions	1–8
How clients rated their experience of receiving counselling	1–7
Proportion of adopters or switchers who chose a LAPM following their FP counselling session and reported still using the same method at 4 months	1–9
Proportion of adopters or switchers who chose a LAPM following their FP counselling session and who report that they plan to continue using their current method	1–9
Proportion of clients who chose any short-acting FP method following their FP counselling and reported still using the same method at 4 months	1–9
Proportion of clients who chose any short-acting FP method following their FP counselling and who report that they plan to continue using their current method	1–9
How clients rated their overall satisfaction with the FP method they received following their FP counselling at 4 months	1–8

*FP* family planning, *LAPM* long-acting or permanent method of contraception, *MSI* Marie Stopes International

Covariates: (1) country (Ethiopia or Vietnam), (2) client age, (3) client education level (none, primary, secondary, college or higher), (4) marital status (single or no regular partner, regular partner, married, divorced or separated, refused to say), (5) FP intentions (trying to become pregnant now or within 1 year, aiming to become pregnant within 2+ years, do not want any or anymore children or do not know), (6) current FP usage (currently use LAPM, currently use short-acting or natural method or unsure what method, not currently using any FP method or have never used any FP method), (7) reason for visiting MSI clinic (seeking FP health care, seeking abortion health care or seeking other health care), (8) overall initial rating of FP counselling experience (1–5, where 1 is “bad” and 5 is “good”), (9) overall rating at 4 months of satisfaction with the method received (1–5, where 1 is “bad” and 5 is “good”)

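### Fertility intention and current method use are recorded only after counselling, with no pre-counselling reference time, yet both enter the adjusted model that decides the primary outcome

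*Protocol article*

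**What the plan says.** All references are to the protocol article.

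**When covariates are collected.** Quantitative data collection and management states: "There will be three data collection processes, all conducted by researchers". These are the exit telephone interview, the 4-month telephone interview and the observation survey. Client covariates come from the first, on the same form as the outcomes: "as well as a range of relevant socio-demographic covariate data, researchers will conduct initial client exit telephone interviews using a data collection form". Participants, recruitment and consent places that interview after counselling: "Those who agree will then be telephoned in the next 2 days by a researcher for an exit interview". Up to two repeat calls may make it later. Before the interview, clients are asked only whether they may be telephoned. Clinic records are not offered as a general source: "As MSI client data currently collected by clinics are not available for research, we prepared data collection tools". For clients lost to follow-up, records supply basic demographics and chosen method, but not prior intention or prior use.

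**Which covariates.** Table 1 adjusts the primary outcome for covariates 1 to 8. Its legend gives the fifth as "5) FP intentions (trying to become pregnant now or within 1 year, aiming to become pregnant within 2+ years" and the sixth as "6) current FP usage (currently use LAPM, currently use short-acting or natural method or unsure what method", each followed by further categories. Neither is tied to a time before counselling.

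**How they are used.** Statistical analyses fits a first-stage logistic model to the covariates without treatment, then compares cluster-level residuals between arms. Primary inference rests on this adjusted result, partly because it is expected to be less biased than the crude one.

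**What DCA does.** The Abstract attributes the expected rise in LAPM uptake partly to systematic exploration of fertility intentions. The Intervention section says "DCA is designed to prompt the provider to identify each client’s fertility intentions, medical eligibility and individual preferences".

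**The concern.** Covariate adjustment protects a randomised comparison when the covariates cannot be influenced by treatment. Here two of them are measured after treatment, and one, fertility intention, is a subject the intervention makes the provider explore. If DCA changes what women say about their intentions, part of its effect on uptake runs through that covariate. A first-stage model without treatment credits that part to the covariate and removes it from the residuals.

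Covariate 6 raises a different question. Taken literally at the time of the call, a woman fitted with an implant on the day of her visit currently uses a LAPM. The covariate would then partly be the outcome.

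At stake is the result on which the trial's conclusion is declared. The sample size gives almost exactly 80% power for 10.5 points, and the same 10.5 points is the threshold for clinical significance, so there is little room for attenuation.

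**Working it through.** **1. The plan's own figure.** Inputs from Sample size: uptake 0.40 v 0.505, 75 clients per clinic, coefficient of variation 0.2, 18 v 17 clinics. Two-sided 5% is from Statistical analyses.

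c = 1 + (1.960 + 0.842)² × [0.40×0.60/75 + 0.505×0.495/75 + 0.2²(0.40² + 0.505²)] / 0.105²
= 1 + 7.849 × 0.02313 / 0.011025 = 17.47 clinics per arm, against an average of 17.5 available.

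Power is 80.2%. The stated 80% reproduces, so the sample size is not in question.

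**2. Covariate 5, illustration.** Assumptions, none of them from the document:
- a binary intention with 40% prevalence before counselling;
- uptake 30 points higher in women with that intention;
- DCA raises the stated intention by s, and the total effect stays at 10.5 points;
- all 75 clients per clinic enter the analysis.

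With one binary covariate, the first-stage predictions are the pooled group means, so

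adjusted difference = 0.105 − B × s, where B = 0.30 + (0.105 − 0.30s) × s·w(1−w) / [M(1−M)], w = 18/35 and M = 0.40 + s·w.

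| Shift s | B | Adjusted, formula | Adjusted, simulated | Power, simulated |
|---|---|---|---|---|
| 0.05 | 0.305 | 0.090 | 0.091 | 71% |
| 0.10 | 0.308 | 0.074 | 0.073 | 51% |
| 0.20 | 0.309 | 0.043 | 0.041 | 20% |

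The simulation ran the two-stage residual analysis on 400 trials per scenario. Crude power in the same runs was 80 to 81%. With s = 0 the formula returns 0.105. Adjusting for the pre-counselling value of intention also gave 0.105, with power 81 to 84%, so adjustment itself does no harm; the timing does.

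**3. Covariate 6, only if read literally.** Let a share r of LAPM choosers be recorded as current LAPM users at the call, and assume 10% used one before. Pooled uptake is 0.40 + 0.105 × 18/35 = 0.454. For r = 0.5:
- uptake in recorded users: 0.454×0.55 / (0.454×0.55 + 0.546×0.10) = 0.821;
- uptake in the others: 0.454×0.45 / (0.454×0.45 + 0.546×0.90) = 0.294;
- difference between arms in recorded use: 0.9 × 0.5 × 0.105 = 0.047;
- adjusted difference: 0.105 − 0.527 × 0.047 = 0.080.

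The simulation also gave 0.080 for r = 0.5, and 0.101, 0.095 and 0.036 for r = 0.10, 0.25 and 0.90. If no client used a LAPM before, r = 0.5 gives 0.068.

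**4. Is the literal reading likely?** Primary outcome defines switchers and adopters by use at the time of counselling, so the exit form has to ask about that. Every woman in the primary analysis chose a method after counselling. The covariate 6 category for women who have never used a method would therefore be almost empty if it described status at the call. Both facts point to use on arrival.

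**The case against.** A reader might infer that covariate 6 records the outcome and that the adjusted effect could fall close to zero. The document does not support that. The switcher/adopter definition and the never-used category indicate status on arrival, and the Intervention section uses current method in that sense. What stands is that the legend does not say so.

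A reader might also infer that DCA does change fertility intention. The Intervention section speaks of identifying intentions, and the Background describes greater readiness to accept a LAPM, not a changed wish for children. No figure for a shift is given. This limits the size of the concern but does not remove it: an intention stated after a structured discussion of intentions may differ from one stated before.

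Differential recall of prior use between arms is likewise only a possibility. Clients recall their own method over about two days and the interviewers are blinded to allocation, although the clients are not.

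The interview form is not shown and may already ask about status before the session. That is a fair limit. The article itself, however, fixes the covariates, their source and their decisive role, and names no reference time.

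Crude results are also reported, so a large attenuation would be visible. This mitigates the problem without resolving it, because inference rests on the adjusted result. Finally, clients are recruited after clinics are randomised, so intention also guards against case-mix differences. That is a reason to keep it in a sensitivity analysis.

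**Conclusion.** The point holds in a limited form. Covariates 5 and 6 are collected after counselling, have no stated pre-counselling reference time, and enter the decisive model. For covariate 5, if DCA shifts stated intention by 5 to 20 points and intention carries a 30-point association with uptake, a true 10.5 points would appear as about 9 to 4. Both quantities are assumptions, and with no shift this bias is absent. For covariate 6 the likely defect is ambiguous wording; attenuation follows only if the newly chosen method is recorded as current use. The claim of reduced bias for the adjusted analysis is therefore not secured for these two covariates.

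**What to change.** 1. Define covariate 6 from the same item that determines switcher/adopter status: use at the time of counselling, before any method was chosen.
2. Word covariate 5 in the exit interview as intention on arrival at the clinic, before speaking to the provider.
3. Before analysis, prespecify a decisive model limited to variables counselling cannot change: country, age, education, marital status, reason for visit and pre-counselling use. Add covariate 5 in a sensitivity analysis. This matters most for clients already interviewed, since Trial status says recruitment began in January 2017. The list also leaves out covariate 8, the rating of the counselling, which is post-counselling by definition and a separate matter.

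The cost is a wording change, a little precision, and less control of case-mix differences in intention, which the sensitivity analysis would show. Collection at reception is not required. It would gather research data through clinic staff before the telephone consent.
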